## Abstract

**Background:**

Kerala is known as the diabetes mellitus (DM) and hypertension (HTN) capital of the world, thus compelling health professionals to model strategies, addressing their social, behavioural, and cognitive risk factors and eliminating various barriers to management. This paper describes the protocol of our study that aims to examine the effectiveness and sustainability of an integrated care model for the management of chronic conditions and their risk factors through a family-based intervention. The proposed care model targets to modify systems and processes that predispose to chronic conditions by enhancing social cohesion and social networks, preventing lifestyle risks, developing iterative cognitive interventions, and engaging the family into customised treatment adherence strategies navigated by community health social workers (CHSWs).

**Methods:**

A cluster randomised controlled trial (RCT) in selected participants will be conducted involving additional assessments prior to the baseline assessment. The assessment will identify and categorise patients into four risk groups, namely behavioural, social, cognitive, and multiple, based on dominant risks identified. Eligible participants will be randomly allocated (at a ratio of 1:1) into the intervention or control arm. The intervention arm will receive social, behavioural, and cognitive or multiple interventions corresponding to the identified risk groups, whereas the control arm will receive general intervention. Both the groups will be followed up at 6 months and 12 months post baseline to measure outcomes. The primary outcome will be the control of HTN and DM, and secondary outcomes include decreased depression and anxiety and improved functioning, social cohesion, and social network linkages. The sustainability and scalability of this intervention will be assessed through cost effectiveness, acceptability, and user friendliness of the integrated approach by performing a qualitative evaluation.

**Discussion:**

This RCT will inform the potential paradigm shift from a medical model of chronic condition management to a multidimensional, multisystem, and multidisciplinary convergence model navigated by CHSWs. Such a model is not currently considered in the management of chronic conditions in Kerala.

**Trial registration:**

Trial has been prospectively registered on Clinical Trial Registry of India- CTRI/2020/12/029474 on 1st December 2020.

## Background

The poor control status of patients [1] resulting from factors such as a lack of an integrated healthcare system and poor adherence to prescribed treatment recommendations and medications [2] is the key reason for an increase in non-communicable diseases (NCDs). Among these factors, treatment adherence and the management of behavioural or lifestyle risk factors, such as smoking and tobacco use, sedentary lifestyle, poor diet, and alcohol abuse [3], are potentially amenable. Various social risk factors such as poverty [4], a lack of social inclusion and support [5], low social class, low income, and low education levels [6] are other barriers to treatment adherence and behavioural risks. In addition, the non-diagnosis of a chronic condition due to a lack of awareness and deficient healthcare access [7] can be considered a social risk factor.

Patients’ poor control status demonstrates the urgency in directing our interventional focus on treatment adherence [8]. Recent studies have found that social and behavioural risk factors predispose to non-adherence to treatment [9, 10].

The name of our intervention programme is Swāsthya, which is a unique concept from Sanskrit denoting a holistic and integrated approach to the health and well-being of the body, mind, and soul. Swāsthya is an integrated chronic condition management programme based on cross-sectional data collected from a semi-urban community on various behavioural, social, and cognitive risks of chronic conditions, namely diabetes mellitus (DM) and hypertension (HTN). This intervention model specifically targets social factors that are amenable to modification by healthcare practitioners working within the existing health system. We performed a rapid systematic review to critically explore existing models and modifiers. The absence of evidence highlights the need to develop a contextually relevant and theoretically driven intervention model for a community population. This intervention is modelled on the basis of the results of several phases of intervention development, namely scoping review [11], community survey [9], rapid systematic review, and qualitative interviews with patients with HTN or DM and health professionals in the community health ecosystem. This stakeholder-driven model explores behavioural, social, and cognitive factors clustered within individuals, families, and communities in Kerala.

The behavioural risk group was characterised by the following unhealthy habits and physical risk factors: unhealthy diet with a high level of sugar, oil, and salt intake; irregular and frequently erratic food patterns; a high level of alcohol consumption; smoking; and sedentary lifestyle.

The social risk group was characterised by inadequate family support, social isolation, financial distress, and a lack of meaningful social and interpersonal relationships. The social isolation of this group limits their access to health services and deprives them of healthy lifestyle educational resources. Financial distress is a significant but modifiable social risk factor that predicts noncompliance to treatment.

Stakeholders, particularly community health professionals, highlighted poor public awareness of the importance of adherence to medication and a lack of public awareness of government services, such as NCD clinics, as the most important barriers to treatment adherence. In addition, a misconception exists that the quality of privately purchased medications is higher than that of government-subsidised medications provided at primary health centres (PHCs).

Health professionals, particularly PHC doctors, suggested task shifting as the potential method to improve the management of risk factors for cardiovascular disease (CVD)in an integrated service delivery ecosystem, especially in the context of overcrowding and rushed consultations at PHCs. Moreover, they suggested that a care model should have a pyramidal platform wherein the system can categorise patients based on their care needs and establish a referral pathway to ensure the maximum coverage of services at a minimum cost; this type of model can be best suited for low- and middle-income countries (LMICs) such as India. In addition, the health professionals indicated that Accredited Social Health Activists (ASHAs), if trained, can deliver health education services including formal and informal resource linkage functions, social connectedness, and initial mental health screening.

Addressing the lack of family and other support for people with chronic diseases and providing psychological support are crucial to address the barriers to the management of risk factors for CVD. According to health care professionals, for a complex social intervention to be successful in India, it needs to account for resources in families and communities and its social context. Strengthening weak ties in people’s networks is crucial to connect them to health resources and public health communication.

This intervention aims to develop and implement a sustainable and cost-effective family-based [12] care package to address barriers to treatment adherence by utilising already existing human health resources. ASHAs, an untapped community-based health resource [13] are equipped to provide the care package based on the priorities of patients through task-shifting and task-sharing strategies. The uniqueness of this family-based, community-focused intervention model based on theory of change (ToC) is that community health social workers (CHSWs) play a key role to navigate change pathways by utilising their professional knowledge and competencies.

## Methods/design

### Aim of the study

The goal of this intervention is to improve treatment adherence and medical compliance by addressing social, behavioural, and cognitive barriers to ensure the control of chronic conditions such as HTN and DM. The objectives of the current intervention are as follows: 1) to allocate patients to various risk groups (behavioural, social, cognitive, and multiple) based on their exposure to dominant risk factors; 2) to implement a customised intervention programme specific to each risk group of patients to reduce their determined risk factors; 3) to assess changes in HTN and DM by making changes in behavioural factors, such as smoking, alcohol consumption, diet, and physical activity, social factors, such as social cohesion and social linkages with networks, and cognitive factors, such as reduction of depression and anxiety; and 4) to understand the feasibility and applicability of the ASHA-worker-delivered, social-worker-coordinated, integrated, health care model for the management of HTN and DM.

### Study design and setting

This is a two-arm cluster randomised controlled trial (RCT) designed to be executed in patients with DM or HTN in association with government-run PHCs and the existing public health ecosystem in Kerala, India. This study will be conducted in Ernakulam district, Kerala, India, with active support from University of York, United Kingdom, and University of Melbourne, Australia. The Ernakulam district is administratively divided into seven main revenue divisions, and Aluva is one of them [14]. The Aluva division is further divided into different units called panchayats (with approximately 25,000–30,000 people residing in each panchayat and each panchayat is further divided into different wards with approximately 1000 to 1500 people residing in each of them), and one panchayat from the Aluva division is selected for the intervention. PHCs and ASHA workers assigned to these geographical units will assist the execution of the intervention. ASHA workers are a network of community health workers who are often selected from the same community; thus, they have the acceptance and trust of the community people. A list of ASHA workers consenting to participate in this study will be prepared, and 10 of them will be randomly selected using computer generated random numbers for providing the intervention. Their assigned wards will be considered as intervention clusters for the current trial. A list of patients with DM or HTN from the selected wards will be obtained from the PHC registry through ASHA workers, and household interviews will be conducted for data collection. Three data collection time points are planned for both the arms: one at baseline and then after 6 months and 12 months after baseline.

Two levels of randomization will be employed in this study. Of the 10 ASHAs, 5 will be randomly allocated either to the treatment intervention arm (Swasthya intervention) or the usual care arm (no interventions other than detailed assessments). Computer-generated random numbers generated by an independent person who is not involved in the study will carry out the randomization of the ASHA workers to either group. Randomization of ASHAs and their clusters will be performed only after the collection of complete baseline data. Their assigned wards will be considered as intervention clusters for the current trial. To eliminate the possibility of contamination, these two groups of ASHA workers will be given training and orientation separately and each of them will be concealed by the group to which they belonged. Independent persons will do the outcome assessment and manage the data to ensure blinding to the Intervention content and its processes. The data analysts will receive the data only after locking the database.

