#### Primary outcomes

Primary outcomes include an improvement in risk factor control status (BP < 140/90 mmHg and fasting blood glucose < 110 mg/dL) and abstinence from smoking or tobacco use.

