### Sample size

In the community, 36.33% people aged more than 30 years were found to have HTN and/or DM [9]. Thus, this cluster RCT will include 1452 participants and their families (726 patients in each arm). Trained and certified project staff will collect baseline data by using study questionnaires. Project staff, under the supervision of the principal investigator, will complete data entry into computer systems. The data will be collated, cleaned, and analysed centrally. Furthermore, the accuracy of data entry in randomly selected fields will be independently checked by the principal investigator of the study.

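### Ten wards are split 5:5 after baseline data are complete, but no balance constraint using those data is stated; constrained randomisation would be a cheap improvement

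*Protocol article*

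**What the plan says.** All of the allocation text is in the Protocol article, Study design and setting.

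- **Units and ratio:** "Of the 10 ASHAs, 5 will be randomly allocated either to the treatment intervention arm", and the other five form the usual care arm. Each worker's ward is a cluster.
- **Mechanism:** computer-generated random numbers, produced by someone independent of the study, "will carry out the randomization of the ASHA workers to either group".
- **Timing:** "Randomization of ASHAs and their clusters will be performed only after the collection of complete baseline data".

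The article names no stratification, matching, minimisation or other balance constraint. The 5:5 split is the only restriction.

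Under Study outcomes, blood pressure, blood sugar and body mass index are measured in all participants at baseline. Statistical analysis plans comparison of changes from baseline, a mixed effect analysis of covariance with a time-by-group term, and adjustment for confounders that it does not name. Under Sample size, "this cluster RCT will include 1452 participants and their families (726 patients in each arm").

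**The concern.** With ten clusters, randomisation cannot be relied on to even out the arms. Ward-level differences in control, blood pressure or size can fall mainly on one side by chance. Most cluster trials must allocate before they have the data to prevent this. Here the order is favourable, because every ward's baseline values will exist before the draw, yet the stated procedure does not use them at that step.

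What is at stake is precision, and how convincing the result looks. A visible baseline gap in control of several points, in a trial of ten wards, would make readers doubt any difference of similar size at 12 months. Adjustment afterwards helps, but the effect estimate still pays for the imbalance that it corrects. The option also lapses once the wards are allocated.

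**Working it through.** **Inputs from the article.** Ten wards, five per arm; 726 patients per arm, so 726/5 = 145.2, taken as m = 145 per ward.

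**Assumed inputs.** The article gives no ICC and no baseline control rate. I take ICC 0.01, 0.02 and 0.05, and control p = 0.3633 or 0.40. The value 0.3633 is only a convenient number: the article's figure is disease prevalence ("36.33% people aged more than 30 years were found to have HTN and/or DM"), not a control rate.

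**Step 1, number of splits.** C(10,5) = 252.

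**Step 2, chance imbalance under the stated scheme.** The standard deviation (SD) of the arm difference is √{2p(1−p)[1+(m−1)ICC]/(5m)}. The mean absolute difference is SD × √(2/π). For example, at p = 0.3633 and ICC 0.01 the design effect is 1 + 144 × 0.01 = 2.44, and SD = √(2 × 0.2313 × 2.44/725) = 3.95 points.

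| ICC | Design effect | SD (points) | Mean absolute difference | Chance > 5 points | Chance > 10 points |
|---|---|---|---|---|---|
| 0.01 | 2.44 | 3.95 | 3.15 | 20.5% | 1.1% |
| 0.02 | 3.88 | 4.98 | 3.97 | 31.5% | 4.4% |
| 0.05 | 8.20 | 7.23 | 5.77 | 48.9% | 16.7% |

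At p = 0.40 the SDs are 4.02, 5.07 and 7.37, and the chances of exceeding 5 points are 21%, 32% and 50%. The assumed control rate therefore matters little and the ICC matters a lot.

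**Step 3, constrained draw.** I simulated sets of ten wards (beta-binomial, m = 145, p = 0.3633), enumerated all 252 splits, and drew one either from all of them or from the best-balanced 100. The three-variable case treats the variables as independent. Entries are the mean absolute difference in baseline control, with the chance above 5 points in brackets.

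| ICC | Any 5:5 split | Best 100, one variable | Best 100, three variables |
|---|---|---|---|
| 0.01 | 3.2 (20%) | 1.1 (0%) | 2.0 (3%) |
| 0.02 | 3.9 (31%) | 1.3 (0%) | 2.5 (10%) |
| 0.05 | 5.9 (50%) | 2.0 (2%) | 3.6 (27%) |

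**Step 4, effect on the estimate once baseline is adjusted for.** With ward-level covariance adjustment, the variance is σ²(1/5 + 1/5 + d²/SS), where d is the arm difference in the baseline covariate and SS its within-arm sum of squares on 8 df. For normally distributed ward values, E(d²/SS) = 0.4/6 = 0.067. Imbalance therefore inflates the variance by 1 + 0.067/0.4 = 1.167 and the SD by √1.167 = 1.080. Perfect balance would thus cut the SD by at most 1 − 1/1.080 = 7.4%.

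Simulation used p = 0.40, ward effects correlated 0.5 or 0.8 over time, participant-level correlation 0.5, and the best 100 on baseline control. The SD of the estimate fell as follows:

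- Correlation 0.5: 3.76 to 3.50, 4.77 to 4.43 and 6.89 to 6.42 points at ICC 0.01, 0.02 and 0.05.
- Correlation 0.8: 3.19 to 2.98, 3.76 to 3.52 and 5.12 to 4.75 points.

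These are cuts of about 6–7%.

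**Step 5, permutation test.** A split and its mirror image have the same balance score, so retained splits come in pairs. The smallest two-sided p-value is 2/252 = 0.008 with all splits and 2/100 = 0.02 with 100 retained. With 26 retained it would be 2/26 = 0.077, which could never reach 5%.

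**The case against.** Simple 5:5 cluster randomisation is a valid design, and nothing in the article is wrong or contradictory on this point. The baseline values are not ignored: Statistical analysis compares changes from baseline and adjusts for confounders, so a baseline gap does not pass straight into the effect estimate. Once that adjustment is counted, the gain from constraining is single-digit per cent (Step 4). Adjustment at participant level also need not use up the 8 between-ward degrees of freedom, so lack of room to adjust is a weak argument. The article is condensed, and the full protocol may describe a constraint.

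Most of this stands and sets the size of the point. The last part stands only in part: the article does set out who randomises, how, when and in what ratio, which is where a constraint would normally be named.

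A reader might infer more than the article supports:

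- **That a large imbalance is likely.** For one outcome, a gap above 5 points only approaches even odds at ICC 0.05, and a gap above 10 points stays below 18% at every ICC tried. The primary outcome has several parts ("improvement in risk factor control status (BP < 140/90 mmHg and fasting blood glucose < 110 mg/dL) and abstinence from smoking or tobacco use"). If three parts are taken as independent at 40%, the worst of them exceeds 5 points in 50%, 69% and 87% of draws at ICC 0.01, 0.02 and 0.05, but that too rests on assumed values.
- **That constraining removes imbalance at no cost.** It reduces imbalance in the chosen variables only, and it binds the analysis.
- **That neighbouring wards in opposite arms are part of this problem.** The article says "one panchayat from the Aluva division is selected for the intervention" but gives no map or adjacency, and contamination is a separate question from balance.

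**Conclusion.** The point holds as a cheap improvement to a valid design. The allocation described does not use baseline data that will already be in hand. Under the assumed ICC of 0.01 to 0.05 and 36–40% control, the chance arm difference in baseline control averages about 3 to 6 points and exceeds 5 points in about 20% to 50% of draws. A constrained draw brings the average to about 1–2 points with one variable or 2–4 with three. It reduces the SD of the baseline-adjusted estimate by roughly 6–8% with one variable; the gain with three was not calculated.

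It would go too far to say that the trial is biased or its test invalid without a constraint. Chance imbalance after proper randomisation costs precision and credibility only. The figures depend mainly on the ICC, which the article does not give.

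**What to change.** Before the wards are allocated, have the independent person:

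1. list the 252 splits;
2. score each on a few prespecified ward-level baseline variables, for example control rate, mean systolic pressure and number of participants;
3. keep about the 100 best balanced;
4. draw one of these at random.

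State the variables, the score and the number retained in the protocol. Adjust for the same variables at participant level in the primary analysis, and restrict any permutation test to the retained set.

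Before glucose control is used for balancing, reconcile Study outcomes, which describes a random glucose measurement, with Primary outcomes, which defines control by fasting glucose. Blood pressure and ward size are not affected by that discrepancy.

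The cost is one short script and a few sentences, with no new data collection. The downsides are the coarser permutation test (smallest two-sided p-value 0.02 instead of 0.008) and an analysis that must respect the constraint. If the full protocol already constrains the draw, a sentence saying so closes the point.

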### Participant recruitment and study procedure

Participants for the trial will be recruited according to eligibility criteria. Eligible families will be those with at least one family member with a confirmed diagnosis of HTN and/or DM. The medical records of the patient will be used to confirm the diagnosis. Informed consent will be obtained from all adult family members. In addition, family members must be either first-degree blood relatives or spouses of the patient. Bedridden and terminally ill patients will be excluded from the study. Participation will be completely voluntary and can be withdrawn at any point if they intent to.

#### Recruitment of participants

The recruitment of participants will be conducted in three stages as follows (Fig. 1).

**Fig. 1 Fig1:**
[figure not shown]
Assessment Schedule of Enrolment, Interventions and assessment

##### First‐level assessment and recruitment

PHCs, with the help of ASHA workers, conduct annual surveys in their respective clusters to collect the information of people with chronic conditions. They collect information on sociodemographic factors such as house number, name, address, phone number, age, sex, type of house, socioeconomic status, education level, occupation, marital status, and receipt of pension, and health factors, such as whether a person has HTN, DM, high cholesterol, thyroid, any disability, or any other chronic condition. This list will be obtained from PHCs through ASHA workers for easy identification of the targeted population. The households of people with DM and/or HTN will be recruited for the next-level assessment. This first-level assessment will be supervised by CHSWs.

##### Second‐level assessment

ASHAs will perform the second-level assessment of the recruited participants. The second-level assessment consists of questions assessing various behavioural, social, and cognitive risks of participants. On the basis of major risk indicators determined through the assessment, CHSWs will categorise the participants into three risk groups, namely behavioural, social, and cognitive. Participants who fall into more than one risk group will be separately categorised into the multiple risk group.

